#### Process evaluation

For the day-care centres in the intervention group, after the first survey, we will analyse the scores on determinants of implementation within the centre and between the centres. Based on the results, we will assess how well these centres score on determinants and we will draft recommendations on how, i.e., exemplary strategies, to address determinants, which score 3 or lower. After the second survey, we will compare scores between the centres. We will assess which centre overall scores highest and/or made the largest improvement in scores on determinants for implementation. Also, we will assess which centre overall scores the lowest on determinants for implementation. Moreover, we will combine this data with data on self-reported use of the exergames by patients, to select two to four centres to interview. Notes of the in-depth interview will be made. Audio recordings will be made of the conversations during the focus groups. These tapes will be transcribed verbatim and these transcripts will be thematically coded regarding factors influencing the implementation of exergaming independently by two members of the research team and then summarized.

#### Economic evaluation

The primary outcome in the economic evaluation will be QALYs. In addition, the economic evaluation will be done for the primary outcome measures of the trial: physical activity and physical functioning using the (SPPB) [55]. Bivariate regression analyses will be done to estimate the differences in costs and effects between the groups. If necessary, costs and effects will be adjusted for confounders. Incremental cost-effectiveness ratios (ICERs) will be calculated by dividing the difference in total costs between the two groups by the difference in effect. Bias-corrected accelerated bootstrapping with 5000 samples will be used to estimate statistical uncertainty. The bootstrapped cost-effect-pairs will be plotted in a CE plane and ‘cost-effectiveness acceptability curves’ will be estimated.

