## Methods

### Study design and setting

We will study the effectiveness and cost-effectiveness of exergaming in a cluster RCT using a randomized controlled block design. All aspects of this trial (design, conduct, and reporting) will adhere to the requirements of the SPIRIT statement (Standard Protocol Items: Recommendations for Interventional Trials) [45, 46] as well as to the Consolidation Standards of Reporting Trials (CONSORT) guidelines [47]. A completed SPIRIT checklist of our trial protocol is available upon request. We will compare people with dementia (and their informal caregivers), who visit day-care centres which offer exergaming to people with dementia (and their informal caregivers), who visit day-care centres that offer regular activities regarding the following outcome variables: physical activity, mobility and physical, cognitive, emotional and social functioning, quality of life of people with dementia and their informal caregivers, experienced burden and positive care experiences of the informal caregivers, and societal costs. The comparator of regular activities at day-care centres without exergaming has been chosen, to ensure that any between-group effect we will find, can be contributed to the exergaming intervention.

Interviews and tests will be scheduled at the start of the study (baseline), after three and after 6 months (two follow up measurements). In total, 24 day-care centres will be recruited. All day-care centres are located in the Netherlands, there are no restrictions to which parts of the country. A list of the study sites will be available upon request. The process analysis will only be carried out in the experimental group.

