**Fig. 1 Fig1:**
[figure not shown]
Flow chart of the randomization of day-care centres

We will (if possible) arrange blocks of centres that are similar to one another (in terms of region and/or target group: i.e. severity of dementia, age of onset, ethnicity, group size in the day-care centre). This is to control for environmental factors that might possibly influence the outcomes. Within these blocks, day-care centres will be randomized by an independent researcher, using Random Allocation Software [48], to either the experimental (exergaming) group or control (regular activities) group (12 day-care centres per group). After randomization, the day-care centres will remain in the experimental or control group throughout the duration of the trial.

Day-care centres which already have the required exergaming equipment, will be paired up with a comparable day-care centre from the same or another care organization without the equipment. Then they will be randomized as a pair instead of as an individual day-care centre. If this pair is randomized in the experimental group, the day-care centre with the exergaming equipment will participate in the trial. Similarly, if this pair is randomized in the control group, the day-care centre without the equipment will participate in the trial. Day-care centres which do not have any exergaming equipment yet, can also be enrolled for randomization individually if they are willing and able to buy the exergaming equipment needed for the trial. This has to be confirmed, prior to randomization, and is intended to ensure they can still participate when they are randomized to the experimental group.

Day-care centres in both groups will each receive an allowance of at most € 1.125,-. When they recruit eight persons or more. They can decide themselves how they want to spend this, for example to pay their staff for the extra hours they have to put in to participate in the research project. Day-care centres in the experimental group may also put this amount towards the purchase of the exergaming equipment.

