### Sample size calculation

Since a high quality study evaluating the effect of a similar intervention on physical activity and mobility was not available when we were writing our protocol, we used previous results on exergaming regarding one of our secondary outcome measures (memory) for this power calculation [38]. We performed a power analysis based on a power of 80% and a difference of 2 (with a standard deviation of 4.6) between scores on the Mini-Mental State Examination (MMSE) [50]. We chose an Intracluster Correlation Coefficient (ICC) of 0.05. This resulted in a sample size of 166 participating dyads with an alpha of 0.05. When also taking into account the cluster effect of the day-care centres (7 dyads per cluster) and drop out (4%), the total sample size needed is 224 dyads.

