### Analysis of the data

#### Effect evaluation

Descriptive statistics at baseline will be used to compare participants with dementia, informal caregivers and staff of day-care centres in the experimental group with the control group. This will provide information on the differences between the intervention and control group at the start of the study.

The baseline scores of the people, who drop out of the study will be compared to those, who remain in the study. This will provide information about selective drop-out. Participants, who drop out during the trial will be included in the main analysis by imputing their scores using multiple imputation.

The effectiveness of the intervention will first be examined by comparing percentages, or mean scores (Chi-Square test, Mann-Whitney U test and T-tests (*p* < 0.05). Second, we will use mixed model regression analysis which will take into account the effect of clustering on the level of the day-care canters, confounders and missing data. The regression analysis will be conducted in three steps. Firstly, an analysis will be carried out for the primary and secondary outcome measures. If any differences in variables related to the outcome measures between the experimental group and the control group are found at baseline, these are added as potential confounders to the model for each outcome measure to check whether the uncorrected Beta-coefficient (β) changes with more than 10%, which means that this variable will remain in the model as a confounder. Examples of potential confounders are type of exergaming equipment, amount of support from staff, severity of dementia etc. Finally, mixed model analysis will be conducted for each outcomes variable for both follow up measurements (three and 6 months) with the selected confounders included in the analysis.

The method of QUalitative INteraction Trees (QUINT) [63] will be used for subgroup analysis. This allows for the identification of subgroups for whom the effect of the intervention differs, for example differences related gender, age, ethnicity or severity of dementia. Cut-off values do not need to be defined beforehand. Based on the QUINT analysis, more specific advice can be formulated with regard to which type of participant or informal caregiver the intervention has a positive effect or not.

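### The economic evaluation names a regression and a bootstrap without any stated allowance for centre clustering, and leaves adjustment of QALYs for baseline utility conditional

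*Protocol article*

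**What the plan says.** The Protocol article describes one cluster-randomised comparison that serves both aims: "We will study the effectiveness and cost-effectiveness of exergaming in a cluster RCT using a randomized controlled block design" (Study design and setting). The same section adds "In total, 24 day-care centres will be recruited", and the randomisation text gives "12 day-care centres per group".

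Clustering is recognised in two places. The Sample size calculation uses an ICC of 0.05 with 7 dyads per cluster. The Effect evaluation, after a first round of simple tests, moves to "mixed model regression analysis which will take into account the effect of clustering" at centre level.

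The Economic evaluation, under Analysis of the data, sets out a separate method in three statements:
- The comparison of arms: "Bivariate regression analyses will be done to estimate the differences in costs and effects between the groups"
- The covariates, which are conditional: "If necessary, costs and effects will be adjusted for confounders"
- The intervals and curves: "Bias-corrected accelerated bootstrapping with 5000 samples will be used to estimate statistical uncertainty"

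It mentions no centre term, cluster-robust variance or unit of resampling, and it does not refer back to the mixed model. It covers QALYs and also the trial's primary outcomes, physical activity and the SPPB. QALYs are computed as an area under the curve from utilities (Secondary outcome measures), with the EQ-5D-5L taken at baseline, 3 and 6 months (Tables 2 and 3).

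**The concern.** Physical activity and the SPPB are analysed twice on the same participants: once with the centre in the model, and once by a method in which the centre does not appear. Dyads from one centre share staff, programme and region, so they are not independent. An analysis that treats them as independent overstates the information in the data. The loss would show in the confidence intervals for incremental costs and effects, in the spread of points on the cost-effectiveness plane, and in the acceptability curves. Cost-effectiveness is a named aim, and this paragraph is the only analysis that serves it.

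The second strand is baseline utility. An area-under-the-curve QALY contains the baseline value, so a difference between arms at baseline becomes part of the QALY difference unless it is adjusted for. With 12 centres per arm, chance imbalance is plausible. Recruitment is by staff who are not blinded, and the Discussion itself expects it to be harder in control centres.

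**Working it through.** **1. The plan's own sample size.** Inputs: difference 2, SD 4.6, power 80%, alpha 0.05 (two-sided reproduces the figure), ICC 0.05, 7 dyads per cluster, 4% dropout.

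- n per arm = 2 × (1.960 + 0.842)² × 4.6² / 2² = 83.04, so 166 in total, as stated.
- Design effect = 1 + (7 − 1) × 0.05 = 1.30, and 166 × 1.30 = 215.8.
- 215.8 / 0.96 = 224.8, against 224 stated.

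The figure reproduces apart from rounding, so the plan's own design-effect formula is a fair basis for the next step.

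**2. Dyads per centre.** 224 / 24 = 9.33 recruited per centre, and 9.33 × 0.96 = 8.96 after dropout. Both exceed the 7 used in the sample size.

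**3. Effect of ignoring the centre.** With m dyads per centre, DE = 1 + (m − 1) × ICC. The ratio of correct to naive standard error is √DE. The naive standard error is too small by 1 − 1/√DE. A nominal 95% interval covers 2Φ(1.96/√DE) − 1.

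The ICC of 0.05 was chosen for the MMSE, and none is given for costs or QALYs. The range 0.01 to 0.20 is therefore an assumption.

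| m | ICC | DE | √DE | Naive SE too small by | Coverage |
|---|---|---|---|---|---|
| 8.96 | 0.01 | 1.080 | 1.04 | 3.8% | 94.1% |
| 8.96 | 0.05 | 1.398 | 1.18 | 15.4% | 90.3% |
| 8.96 | 0.10 | 1.796 | 1.34 | 25.4% | 85.6% |
| 8.96 | 0.20 | 2.592 | 1.61 | 37.9% | 77.7% |
| 9.33 | 0.01 | 1.083 | 1.04 | 3.9% | 94.0% |
| 9.33 | 0.05 | 1.417 | 1.19 | 16.0% | 90.0% |
| 9.33 | 0.10 | 1.833 | 1.35 | 26.1% | 85.2% |
| 9.33 | 0.20 | 2.667 | 1.63 | 38.8% | 77.0% |

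At 7 per centre and ICC 0.05, √DE is 1.14 and coverage 91.4%.

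**4. Check by simulation.** Setting: 12 centres of 9 per arm, normal outcome, no true difference, 2000 trials, 500 resamples each, percentile intervals.

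| ICC | Empirical SD of the difference | Mean SE, resampling individuals | Coverage | Mean SE, resampling whole centres | Coverage |
|---|---|---|---|---|---|
| 0.05 | 0.157 | 0.135 | about 90% | 0.153 | 92.7% |
| 0.20 | 0.216 | 0.134 | about 78% | 0.207 | about 93% |

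The simulation agrees with the formula. It also shows that whole-centre resampling with 12 centres per arm removes most of the under-coverage but not all of it.

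**5. Weight of baseline utility.** By the trapezoid rule over two quarter-years, QALY = 0.25 × (u0 + u3)/2 + 0.25 × (u3 + u6)/2 = 0.125 u0 + 0.25 u3 + 0.125 u6. Baseline has 0.125 of a total weight of 0.5, which is 25%. The documents give no size of imbalance, so 0.05 is assumed:

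- baseline term alone: 0.125 × 0.05 = 0.006 QALY;
- imbalance persisting fully at 3 and 6 months: 0.5 × 0.05 = 0.025 QALY.

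The assumption of persistence supplies the other 0.019; the baseline weight does not.

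**The case against.** The strongest reply is that the paragraph is silent on clustering and does not exclude it. This is a condensed article, the analysis plan is not shown, and the resampling unit and covariate list are details that such a plan often carries. The authors clearly know that the design is clustered. Bivariate may also mean that costs and effects are modelled jointly, which is close to the remedy proposed here.

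Part of this stands. A reader might infer that the plan commits to resampling individual dyads, or that its intervals will certainly be too tight; the unit is not stated, so neither can be said. What remains is that the article does not leave the method open. It names a regression type, a bootstrap type and a number of samples, and none of them carries the centre. Joint modelling deals with the correlation between costs and effects, not with correlation within centres.

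On baseline utility, the text speaks of confounders and does not say that baseline values are ignored. If the Effect evaluation's rule applies (variables that differ at baseline are tried, and kept if the coefficient moves by more than 10%), a large utility imbalance would probably be caught. But the economic section does not refer to that rule, and even so the adjustment would depend on the observed data.

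A reader might also infer that, because intervention cost comes from interviews with centre staff, the effective sample for costs is nearer 12 centres than 112 dyads. The documents do not support this. They do not say whether costs are assigned per centre or as an average, and total societal cost also includes care use and informal care recorded for each dyad.

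**Conclusion.** The point holds as a mismatch between a cluster-randomised design and an economic method with no stated allowance for clustering, and it should be fixed. If dyads are treated as independent and an ICC of 0.05 applies to costs and QALYs, the naive standard error is about 15% too small at about 9 dyads per centre, and a nominal 95% interval covers about 90%. The loss is slight at ICC 0.01 (about 94%) and serious at 0.20 (77–78%). These figures assume equal centre sizes and ignore any gain from the blocking of similar centres. The baseline strand is smaller: about 0.006 QALY from the baseline term for an assumed imbalance of 0.05, and 0.025 only if that imbalance persists unchanged. The primary effect analysis is not affected.

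**What to change.** State in the Economic evaluation that:

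- incremental costs and effects are estimated with a centre-level term, either by a bivariate multilevel model or by seemingly unrelated regression with cluster-robust variance and a small-sample correction;
- any bootstrap is two-stage, resampling centres within arm and then dyads within centre, with the note that centre resampling with 12 centres per arm can still under-cover slightly;
- QALYs are always adjusted for baseline utility, whatever imbalance is observed.

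This costs one paragraph and analysis code, with no new data or participants. Intervals will be wider and acceptability curves flatter, in line with the information that the design provides.

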### Harms

#### Risk/benefit assessment

The risk of harm when participating in the exergaming intervention is in our opinion negligible, and comparable to the risk of participating in regular physical exercise activities (or lower, as this is in a safe environment). Although physical injuries cannot be ruled out, we will try to prevent them as much as possible. During the exergaming intervention, a member of staff of the daycare center will be present to supervise. If a daycare center doesn’t have exergaming equipment yet, they are advised about the purchase of the exergaming equipment for people living with dementia and are offered a training in the use of this equipment.

We think the (results of the) research project can have benefits for people living with dementia and their informal caregivers. We hope that, if exergaming proves to yield positive effects, this will result in the intervention becoming available for more people living with dementia. To measure the effects, it is essential to let potential end users themselves try out and evaluate the exergames, and therefore involve them in the research project. In our opinion, the potential benefits of the research project are in balance with the potential risk and burden for people with dementia participating in the trial.

#### (serious) adverse events

Adverse events (AE’s) and serious adverse events (SAE’s) are specified according to definitions the Central Committee on Research Involving Human Subjects (CCMO) [64]. They will be registered and reported to the METc of the Amsterdam UMC, location VUmc / CCMO following the procedure which is described on the CCMO website [64]. All (S)AE’s will be monitored, until the risk of harm is gone or until a stable (end) state has been reached. Depending on the situation, extra tests might be necessary, or a referral to a doctor. The research team will keep an up-to-date overview of all (S)AE’s until the end of the trial.

### Trial status

Recruitment of day-care centres commenced July 2016 and ended in August 2018. Inclusion of participants within the day care centres started with the first interview taking place in February 2017 and was finished in September 2018. At the time of the initial submission of the manuscript, data-collection was still ongoing and should be finished by March 2019. For the process evaluation, the first MIDI list was sent out to day-care centres in the experimental group in July 2017 and the second one in December 2018, and the qualitative interviews regarding implementation issues will take place in the first quarter of 2019. Focus groups are planned to take place in February/March 2019.

### Dissemination policy

Trial results will be communicated to several different target groups: people living with dementia, older people, informal caregivers, volunteers, healthcare professionals (staff of day-care centres, meeting centres, nursing homes), policy makers, managers of care organisations, insurance companies, researchers from various backgrounds (dementia care, game design, movement sciences, psychology, physiotherapy, geriatric medicine and general practice), and companies developing and selling exergames, Each target group will be reached using appropriate communication channels, eg lectures and presentations at different kinds of conferences/meetings, digital newsletters, websites, social media, networks, (scientific) journals, and magazines. Authorship will only be granted to those who contribute to writing a publication. No professional writers will be used for publications, except for language checks in non-Dutch articles.

## Discussion

Large and scientifically robust studies to evaluate the effects of exergaming for people living with dementia are lacking. The aim of this study is to evaluate the effectiveness and cost-effectiveness of exergaming for people living with dementia and their informal caregivers. If the exergaming intervention proves to have positive effects, this may boost the uptake of the exergaming intervention in other day-care centres. Implementation will be supported by the findings from our process evaluation, which will provide extensive information on factors that either promote or hinder successful implementation of exergaming for this target group.

We expect that exergaming will have positive effects on people living with dementia in several domains such as physical, cognitive, emotional, and social functioning, and on quality of life for both people living with dementia and their informal caregivers. We hope that the results of this project will motivate people with dementia to exercise more and as a result to experience positive effects on their wellbeing and the quality of life. We envision that this may have a positive effect on the burden of care experienced by their informal caregiver as well. Finally, we expect that societal costs of the people living with dementia and their informal caregivers are affected.

There are several challenges that lie ahead when starting this research project. Recruitment can be a complicated process with several steps that have to be taken. Firstly, day-care centres have to be found that are willing to participate and can have funding ready in case they are assigned to the experimental group. Secondly, the research team has to effectively collaborate with the local project coordinators of the day-care centres. Successful recruitment can very much depend on this collaboration as well as whether the local coordinator is able to motivate visitors of his/her day-care centre (and their informal caregivers) to participate in the trial. We will support the staff of day-care centres as much as possible in the process of recruitment, for example by written instructions for the local coordinator of the day-care centre regarding recruitment and motivating participants.

There have been several budget cuts in the healthcare sector in the Netherlands, which puts time pressure on staff of day-care centres. This can negatively impact both recruitment of day-care centres and participants with dementia for our trial. However, our research project partly reimburses day-care centres (both in the experimental and control group) to participate in the trial. In addition, we negotiated a discount on exergaming equipment for them and a list of organizations where they can apply for additional external funding. Finally, staff of participating day-care centres get the opportunity to attend a free training afternoon on how to use the exergaming equipment and to engage in an innovative technology-based intervention.

For day-care centres in the control group, recruitment of participants might be more difficult. Because participants with dementia will not get the intervention, the importance and potential benefit of participating in the study might be less clear to them (and to the informal caregivers). This could make it more challenging for the local coordinator to explain and motivate them to participate. In both the experimental and control group, some informal caregivers might already feel overburdened, and thus might not be willing to participate in the study, because they overestimate the time it will cost them.

With regard to the outcome measures, it is a challenge in the field of assistive technology to select appropriate outcome measures [65]. In our study, some outcome measures may be complicated to assess among people living with dementia. For example, the Intrinsic Motivation Inventory (IMI) [66] consists of a long list of statements and has a seven point scale for answering, which can be confusing. To mitigate this problem, we will use a printed card with the answering scale. Also, certain outcome measures can be challenging if people are deaf, analphabetic or not native Dutch speakers. However, this was not taken into account when we established our in- and exclusion criteria. Furthermore, because of the number of outcome measures, the duration of the interviews can be quite long, especially for people living with dementia, but also for informal caregivers, who are already very busy. To minimize the occurrence of problems during the interviews, interviewers receive a training with extensive instructions. For example, they are instructed on how to assess each outcome measure, but also to look out for and deal with distress during the interview. If needed, the interview can be divided into two shorter interviews during two subsequent appointments instead of one.

Next to the interviews with people living with dementia, we will collect data from the informal caregivers and the staff of day-care centres. This method of collecting data is prone to errors and could easily be forgotten by those involved. To minimize those problems the research team will remind the staff of day-care centres and informal caregivers frequently.

Another limitation of this research project is that merely one type of exergaming is included. Therefore, the research findings can be typical for only interactive cycling and it is not possible to be sure that findings are generalizable among other types of exergames.

This research project is part of the Marie Curie Innovative Training Network (ITN) Interdisciplinary Network for Dementia Using Current Technology (INDUCT). This ITN offers many different perspectives and insights. Various academic research areas are represented, such as psychology, medicine, occupational therapy, nursing, movement sciences, and anthropology. Additionally, people working outside of academia are also part of the network, for example from commercial industry or care organizations. Moreover, both our exergaming research project group and advisory group meet regularly to offer their multidisciplinary input. In terms of patient and public involvement (PPI), an former informal caregiver is part of our project group, and the European Working Group of People with Dementia (EWGPWD) is consulted several times.

In summary, this study will contribute to the evidence base on the effectiveness and cost effectiveness of exergaming for people living with dementia and their informal caregivers. It will also yield information about implementation of exergaming for this target group. If this study demonstrates positive results on physical, cognitive, emotional, and/or social functioning in people living with dementia and on quality of life of people living with dementia and their informal caregivers, this will hopefully contribute to exergaming becoming available for more people living with dementia.

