### Exclusion criteria

Exclusion criteria are as follows. Severe physical disorders or diseases, which would make it impossible for the participant with dementia to take part in an exergaming activity. Terminal diseases (other than dementia).

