### Recruitment

Participants are recruited by the staff of the day-care centres. Each day-care centre has a local project coordinator (i.e. physiotherapist, activity coordinator) assigned among their staff. This person is instructed by the research team on how to recruit participants and supervise the intervention and data collection.

To inform potential participants the project coordinator at the day-care centres offers an information package to the person with dementia and their informal caregiver.

Informal caregivers are offered a small compensation (worth € 25,-) for their participation in the research project. The compensation is meant as an extra motivation for them to take part, especially because informal caregivers can often feel burdened which might refrain them from participating [49]. It is not compulsory to finish the entire data collection trajectory (i.e. all interviews and tests for both informal caregiver and participant with dementia) in order to receive the compensation.

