### Blinding

Due to the design of the study and the nature of the intervention, blinding of staff of day-care centres, participants with dementia and informal caregivers is not possible. Because there are a few different questions in the outcomes measures for the control and experimental group (i.e. questions about the exergaming intervention) interviewers could also not be blinded.

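### Day-care staff appear to recruit dyads with their centre's allocation known, and the protocol expects willingness to differ by arm, so the arms cannot be assumed comparable at entry

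*Protocol article*

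**What the plan says.** The unit of randomisation is the centre: "Within these blocks, day-care centres will be randomized by an independent researcher, using Random Allocation Software" (Recruitment and randomization day-care centres), with 12 centres per arm. Individuals enter through the centre's own personnel: "Participants are recruited by the staff of the day-care centres" (Recruitment). A local coordinator leads this, and the role is not separate from delivery of the trial: "This person is instructed by the research team on how to recruit participants and supervise the intervention and data collection". Existing and new visitors may both join (Participants and setting), so the pool is not closed at randomisation.

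Under Blinding, "blinding of staff of day-care centres, participants with dementia and informal caregivers is not possible", and interviewers are unblinded too. One exclusion concerns physical conditions "which would make it impossible for the participant with dementia to take part in an exergaming activity" (Exclusion criteria).

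The Discussion addresses recruitment by arm directly: "For day-care centres in the control group, recruitment of participants might be more difficult". The reason given is "Because participants with dementia will not get the intervention, the importance and potential benefit of participating in the study might be less clear to them". As for the consequence, it says: "This could make it more challenging for the local coordinator to explain and motivate them to participate".

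Under Study design and setting, the comparator is said to have been chosen so that any between-group effect can be put down to exergaming. Under Effect evaluation, variables related to outcome that differ at baseline are tested as confounders and kept if they change the coefficient by more than 10%.

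**The concern.** Randomising centres balances centres in expectation. It does not balance the people enrolled afterwards if those who invite them, or those who decide whether to accept, already know the arm. In an exergaming centre the invitation includes a new activity. In a control centre it is interviews, tests and diaries around the usual programme. Liking for exercise, cycling history, fitness and caregiver engagement could all affect who accepts, and all plausibly predict physical activity, SPPB and the six-month course. The exergaming exclusion is a practical question in one arm and a hypothetical one in the other.

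A difference at three or six months could then partly reflect who joined. This touches both primary outcomes and every secondary comparison between arms. A larger sample would not remove it.

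**Working it through.** **Was the arm known at recruitment?** The text shown does not state the order, and Figs. 1 and 2, which hold the timelines, are not shown. Four places point the same way.

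1. Discussion: control recruitment may be harder because candidates will not receive the intervention. This requires the arm to be known to recruiter or candidate.
2. Recruitment and randomization day-care centres: where a centre that owns equipment is paired with one that does not, the result decides which of the two takes part. Unless both enrolled in advance, which the article does not say, dyads there enter after allocation.
3. Table 2: satisfaction with the exergaming activity, an item for the experimental group only, is marked at baseline. The arm is therefore known by the first interview.
4. Blinding: staff, participants, caregivers and interviewers are all unblinded.

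**Is there a stated safeguard against differential selection?** The independent randomiser protects the allocation of centres only. Written instructions for coordinators and payments to centres and caregivers bear on numbers. The confounder rule reaches measured variables only, and only those seen to differ at baseline. One of its examples, type of exergaming equipment, is a feature of the intervention and not an entry characteristic.

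**The plan's own sample size.** Inputs from Sample size calculation: difference 2, SD 4.6, power 80%, alpha 0.05 (taken as two-sided), ICC 0.05, 7 dyads per cluster, dropout 4%.

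- Unclustered total: 2 × 2 × (1.960 + 0.842)² × (4.6/2)² = 166.1 (stated: 166).
- Design effect: 1 + (7 − 1) × 0.05 = 1.30, and 166 × 1.30 = 215.8.
- Dropout: 215.8/0.96 = 224.8, or 215.8 × 1.04 = 224.4 (stated: 224).

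The stated figure is reproduced.

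**Illustration of size.** Two inputs are assumptions found nowhere in the documents: exercise-keen people do 0.5 SD better, and their share among recruits is 20 to 40 percentage points higher in the exergaming arm. No adjustment is applied.

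- Bias: 0.5 × 0.20 = 0.10 SD to 0.5 × 0.40 = 0.20 SD.
- Against the planned effect of 2/4.6 = 0.435 SD: 23% to 46%.
- Completers per arm: 112 × 0.96 = 107.5; per centre 107.5/12 = 8.96.
- Design effect: 1 + 7.96 × 0.05 = 1.398; effective n per arm 107.5/1.398 = 76.9.
- SE: √(2/76.9) = 0.161 SD.
- Shifts: 0.10/0.161 = 0.62 SE and 0.20/0.161 = 1.24 SE.
- Two-sided rejection with no true effect, Φ(−1.96 + s) + Φ(−1.96 − s): 0.090 + 0.005 = 9.5%, and 0.236 + 0.001, about 24%.

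With the plan's own design effect of 1.30 the same biases give 9.9% and 25%. If adjustment removed half of the smaller bias, leaving 0.05 SD, the rate would be about 6%.

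**The case against.** The strongest reply has five parts.

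- **Sequence and outcome.** The order is inferred, the timeline figures are missing, and the Discussion says only that recruitment might be harder. This stands in part. A reader might infer that the groups are in fact not comparable. The documents do not support that: no baseline data are shown, and some dyads may have been identified before allocation. That recruitment took place with the arm known, at least in part, remains well supported.
- **Who selects.** A reader might infer that staff hand-pick visitors and apply the exergaming exclusion themselves. The article says staff recruit and the coordinator offers an information package. It does not describe picking, nor say who judges eligibility. The concern needs neither, because arm-dependent willingness is enough.
- **Measured confounders.** Much of what could differ is collected at baseline: exercise interest and enjoyment (IMI), past sports and cycling experience, SPPB, registered activity, PASE, and caregiver competence and positive care experiences. This stands, and adjustment could remove part of any bias. It cannot reach what is unmeasured, and selecting covariates by observed difference and a 10% change is a weak way to use these data.
- **Size.** The bias is assumed, its direction is not established (it could run towards the null), and the reference effect is for MMSE, a secondary outcome. All of this stands, so the figures illustrate and do not estimate.
- **Remedy.** In owner/non-owner pairs, the randomisation rule itself tells each centre which arm its visitors would enter, so withholding the result conceals little. And inclusion finished in September 2018 (Trial status). Both stand and limit what can be fixed.

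**Conclusion.** The concern holds in limited form. Unblinded centre staff appear to recruit with the allocation known, the protocol itself anticipates arm-dependent willingness, and no stated measure addresses differential selection. The arms cannot be assumed comparable at entry, and attributing any between-group effect to exergaming is not secured by the choice of comparator.

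This rests on an inferred order of events. The size is unknown. The range of 0.1 to 0.2 SD, with a false-positive rate of about 10% to 24%, depends on two assumed inputs, a bias favouring exergaming, the planned ICC and dropout, and no adjustment. It should not be read as an estimate for this trial.

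**What to change.** **Design remedy.** Before a centre's allocation is released, its coordinator sends the research team a coded list of all current visitors who meet the criteria. Enrolment is from that list, with consent and baseline before disclosure where feasible. This fits the existing step in which centres confirm, before randomisation, that they can buy the equipment. In owner/non-owner pairs both centres send a list, but concealment there is only partial. The cost is a delay of some weeks. Taking consent and baseline at both centres of a pair would also mean work at a centre that then does not take part.

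**What can still be done, with inclusion complete:**

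1. Flag dyads identified or recruited after allocation, and repeat the primary analysis without them if enough remain.
2. Report eligible, approached and consenting numbers by arm, so far as centres recorded them.
3. Fix in advance, for the primary models, adjustment for the baseline value of the outcome, IMI, and past sports/cycling experience, in place of the baseline-difference and 10% rule. All are already collected.
4. Qualify the attribution statement under Study design and setting, and name selection at recruitment as a limitation.

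Items 3 and 4 need no new data. Items 1 and 2 depend on what the centres and the research team recorded. Adjustment reduces bias from measured traits only, so item 4 is needed whatever item 3 shows.
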